#### Multilevel (mixed) model analysis

3.1.3

Multilevel (mixed) model analysis will be conducted to compare outcomes for both conditions on the OQ-45.2, with baseline scores (T0), scores after 9 months (T1), and at the end of treatment after 18 months (T2) as dependent variables and treatment (FACT or AMBIT) as independent variable. The different levels for the multilevel (mixed) model analysis will be: 1) participant, 2) measurement wave, 3) outcome measure, and 4) location of sampling. A multilevel (mixed) model analysis uses all data and contributes to power in the analysis in contrast to case wise deletion for missing data.

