The primary objective of this study is to investigate the effectiveness of AMBIT for patients with SMI-PD in comparison to treatment with FACT. It is hypothesized that an AMBIT approach will be more effective in improving outcomes on a broad spectrum of life domains (e.g. leisure activities, education, housing, family, symptoms, and drug use) in patients with SMI-PD than FACT.

Furthermore, this study aims to investigate differences in treatment effects of the following secondary variables regarding personality functioning, and social- and societal functioning, mentalizing capacity, epistemic trust, and suicidality. It is hypothesized that patients in the AMBIT condition show greater improvement on a broad spectrum of outcomes, considering psychiatric symptoms, social ecology, relationship networks/qualities, and resiliencies as measured by the instruments included in the present study as discussed in the method section.

Cost-effectiveness will also be evaluated for AMBIT. It is hypothesized that AMBIT will be a more cost-effective treatment than FACT.

Lastly this study aims to investigate variables that may moderate and mediate treatment outcome. It is expected that severity of childhood trauma, and duration of illness have a moderating effect on treatment outcome, while epistemic trust and mentalizing capacity are expected to have a mediating effect on treatment outcome.

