### Design

2.1

This controlled, naturalistic, longitudinal cohort study will follow participants over 18 months of treatment to assess recovery outcomes in patients with SMI-PD across three settings: FACT, AMBIT-PD, and AMBIT informed-MBT. A naturalistic design was chosen to enhance ecological validity and generalizability, allowing treatment to reflect real-world practice rather than rigid protocols. Unlike a randomized controlled trial (RCT), which prioritizes internal validity, this approach better captures treatment effectiveness in complex, real-life settings where patient motivation—key to therapeutic success— will not be affected by randomization (40–43). Since participants must have already been in mental health care for at least two years (6–8), altering their current care for the sake of an RCT may be unethical and disruptive. The flexibility of the AMBIT approach, which focuses on restoring trust and adapting to individual needs, would also be compromised by a rigid study design, potentially increasing epistemic mistrust and disengagement (42). A naturalistic design minimizes exclusion due to strict criteria and reduces drop-out, leading to more complete data. However, the absence of randomization does increase the risk of bias from unknown confounders, which will be considered in the analysis (40, 42–44).

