#### Moderating and mediating effects

3.1.4

To analyse the moderating effect of the factor variable (i.e. severity of childhood trauma and duration of illness) on treatment outcome in both treatment conditions an ANOVA will be performed, with the moderating factors, treatment condition and their interaction term as independent variables and the OQ-45.2 scores as dependent outcomes.

A linear regression analysis will be performed to investigate a potential mediating relationship between the treatment conditions and epistemic trust and reflective functioning.

Furthermore, given potential differences across locations, an exploratory moderation analyses with location as a categorical moderator will be conducted.

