### Secondary analyses

3.2

As for the primary analysis multilevel (mixed) models will be used for evaluation of the course of the ESM outcome variables over time. Since ESM data of each questionnaire is nested within days and again within the measurement period (T0, T1 or T2), measurements cannot be deemed independent, which requires the analysis of the data within a multilevel structure. The different levels for the multilevel (mixed) model analysis will be: 1) participant, 2) measurement wave, 3) outcome measure, and 4) location of sampling.

In order to compare within group differences (AMBIT informed-MBT vs AMBIT-PD) in the AMBIT condition on the primary outcome, multilevel (mixed) model analyses will be conducted to, with baseline scores (T0), scores after 9 months (T1), and at the end of treatment after 18 months (T2) as dependent variables and treatment (AMBIT informed-MBT and AMBIT-PD) as independent variable.

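### The primary mixed model, as written, averages the OQ-45.2 group difference over T0, T1 and T2 and states no treatment-by-wave contrast or baseline adjustment, so it does not test greater improvement

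*Protocol article*

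**What the plan says.** Section 3.1.3 (Multilevel (mixed) model analysis) lists the outcomes as starting "with baseline scores (T0), scores after 9 months (T1" and ending with the scores "at the end of treatment after 18 months (T2) as dependent variables and treatment (FACT or AMBIT) as independent variable". Wave enters only in the list of levels: "1) participant, 2) measurement wave, 3) outcome measure, and 4) location of sampling".

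Section 3.2 uses the same form for the comparison within AMBIT, with "treatment (AMBIT informed-MBT and AMBIT-PD) as independent variable".

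Section 3.1.4 does name an interaction, but between moderator and treatment: "with the moderating factors, treatment condition and their interaction term as independent variables and the OQ-45.2 scores as dependent outcomes". It does not say which OQ-45.2 score is meant.

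The primary hypothesis in the Introduction is that "an AMBIT approach will be more effective in improving outcomes on a broad spectrum of life domains" than FACT. The paragraph on secondary variables expects that "patients in the AMBIT condition show greater improvement on a broad spectrum of outcomes". The Abstract defines T0 as the start of treatment. The Design section accepts that "the absence of randomization does increase the risk of bias from unknown confounders".

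**The concern.** The hypotheses are about change. Change is tested by a treatment-by-wave contrast, or by a follow-up difference adjusted for baseline. A model with three waves as outcomes and treatment as its one named predictor gives a single treatment coefficient: the group difference averaged over all waves. Listing wave as a level does not alter this, because a random wave term leaves the treatment contrast averaged over waves.

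Two things are at stake. First, T0 precedes any treatment effect, so giving it weight pulls a real effect towards zero even if the groups start equal. Second, the groups are not randomised. Any T0 difference that survives matching is counted as treatment effect, and it can create a false benefit or hide a true one.

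**Working it through.** **The plan's own figure.** Section 2.2.1 gives a total of 135 for 90% power with f = 0.25, α = 0.05, three groups and three measurements. It states neither the correlation nor which repeated-measures test was used.

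- Between-group test averaged over waves, assumed ρ = 0.5: λ = f²·N·m / (1 + (m − 1)ρ) = 0.0625 × 135 × 3 / 2 = 12.66 on 2 and 132 df. Power is 0.893, and 90% is reached at N = 138. With ρ of 0.46 to 0.47 the answer is exactly 135.
- Group-by-time interaction: 45 at ρ = 0.5 with the same f, or 126 to 129 under other effect-size conventions or the multivariate test.

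The stated 135 therefore fits the wave-averaged group effect best. Because the correlation is not given, this is a pointer and not proof.

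**Inputs for the model check.** Section 2.2 gives 4 × 40 patients, so 80 FACT and 80 AMBIT. With the anticipated 20% dropout, 80 × 0.8 = 64 per group. Assumptions, not in the document: equal correlation ρ between waves (0.5, range 0.3 to 0.7), SD = 1, complete data on the 64, normal approximation, two-sided 0.05. Let d0, d1, d2 be the AMBIT advantage at T0, T1 and T2 in SD units.

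**Formulas**

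- Treatment coefficient as written: (d0 + d1 + d2)/3, variance (2/n)(1 + 2ρ)/3. At n = 64, ρ = 0.5: (2/64)(2/3) = 0.0208, SE 0.144.
- T0-to-T2 change contrast: d2 − d0, variance (2/n)·2(1 − ρ). This is 2/64 = 0.03125, SE 0.177.
- T2 adjusted for T0: variance (2/n)(1 − ρ²). This is (2/64)(0.75) = 0.0234, SE 0.153.

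**Perfect balance, linear effect** (d0 = 0, d1 = 0.25, d2 = 0.50)

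- As written: estimate (0 + 0.25 + 0.50)/3 = 0.25. Then 0.25/0.144 = 1.73, power about 41%.
- Change contrast: estimate 0.50. Then 0.50/0.177 = 2.83, power about 81%.
- T2 adjusted for T0: estimate 0.50. Then 0.50/0.153 = 3.27, power about 90%.

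| ρ (64 per group) | as written | change contrast | T2 adjusted for T0 |
|---|---|---|---|
| 0.3 | 49% | 67% | 84% |
| 0.5 | 41% | 81% | 90% |
| 0.7 | 35% | 95% | 98% |

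With all 80 per group and ρ = 0.5 the three powers are 49%, 88% and 96%.

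**No treatment effect, but a baseline difference that persists** (d0 = d1 = d2)

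- 0.3 SD: 0.3/0.144 = 2.08, rejection about 55%.
- 0.5 SD: 0.5/0.144 = 3.46, rejection about 93%.
- The change contrast is 0 in both cases and rejects at about 5%.

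**AMBIT starts 0.3 SD worse and gains 0.5 SD more** (d = −0.30, −0.05, +0.20)

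- As written: (−0.30 − 0.05 + 0.20)/3 = −0.05, so a true gain appears as a slight disadvantage, with rejection about 6%.
- Change contrast: 0.20 − (−0.30) = 0.50.

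**The case against.** The strongest defence is that this is a condensed article. Section 3.1.3 does not say that treatment is the sole fixed effect. Section 3.1 speaks of a repeated measures analysis, the sample size is framed as a repeated-measures ANOVA, and section 3.2 ties the primary method to the course of outcomes over time. In repeated-measures usage, time and group-by-time are often taken for granted. This stands as evidence that a time effect may have been intended. It does not settle the matter: the article states both the outcome set and the predictor, repeats them in section 3.2, and names an interaction in section 3.1.4 where it wants one.

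A second defence is matching. Section 3.1.2 aims for pairs that do not differ on observed characteristics, and its variables are given only as examples, so baseline OQ-45.2 is neither named nor excluded. That could shrink d0, but it does nothing about the dilution, which occurs with d0 = 0.

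Three stronger readings are tempting and are not supported:

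- That T0 as an outcome is itself an error. It is not; a model with treatment × wave keeps T0 as an outcome and is sound.
- That the study carries a 55% or 93% false-positive rate. Those rates need the literal model and a residual 0.3 or 0.5 SD difference after matching, and the document gives no such figure. The 5% for the change contrast likewise assumes that the gap would have persisted unchanged. If the groups regress to the mean differently, that contrast is biased too.
- That the moderation ANOVA is wrong and needs a three-way interaction. It is unspecified as to which score it uses, and a three-way term is a preference.

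**Conclusion.** The point holds for the model as written in section 3.1.3 and repeated in section 3.2. The fault is the absence of a treatment-by-wave contrast or a baseline adjustment. Without one, the treatment coefficient is a three-wave average with one third of its weight on the start of treatment, and it does not answer the hypothesis about improvement.

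The firm part is the dilution: a linearly growing effect is halved whatever the correlation and however good the matching. The size of the power loss depends on the assumed correlation, sample size and linear growth. The bias from baseline differences is conditional on what remains after matching, and can run in either direction. If a time effect was intended, the repair only records that intention. Because this is the primary analysis, it should be settled before outcome data are analysed.

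**What to change.** In sections 3.1.3 and 3.2, choose one of two forms and state it:

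1. Fixed effects for wave (categorical), treatment and treatment × wave, with a random participant effect. The primary contrast is the treatment difference in T0-to-T2 change on the OQ-45.2.
2. T1 and T2 as outcomes with T0 OQ-45.2 as covariate. The primary contrast is the treatment difference at T2.

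Either is acceptable. They rest on different assumptions about how a baseline gap would evolve, so the choice should be made in advance.

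In section 3.1.2, list baseline OQ-45.2 among the propensity-score variables. In section 3.1.4, say whether the moderation outcome is T2 adjusted for T0 or the change from T0; a three-way interaction is optional.

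The cost is a few sentences. No extra data, visits or participants are needed.

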#### Feasibility

2.2.2

To map the feasibility of participant recruitment, we rely on the standard guideline of care for personality disorders (45). It is estimated that approximately 30% of the FACT teams meet the criteria for SMI-PD. GGZ Rivierduinen location Leiden has 4 FACT teams. Altrecht location Utrecht has 9 FACT teams. Each team has at least 200 clients in care on a yearly basis. Therefore, approximately 60 clients per FACT team are likely to meet the inclusion criteria of the study, which amounts to around 780 clients (45). As the study is observational in nature and only minimally burdensome for participants (questionnaires), and since we plan to provide a generous participation fee of 30 euros per measurement, we think it is reasonable to expect that around 10% of the clients will consent to participate. From previous naturalistic research (46), it was found that a vast majority (87%) of this target group was willing to participate in research. Rivierduinen has one AMBIT informed-MBT team, whereas Altrecht has five, who each treat 200 to 250 clients, nearly all of whom meet the inclusion criteria of the study, amounting to around 1000 likely eligible participants. Since this also concerns naturalistic research, we are confident that recruiting 80 participants at Rivierduinen and 80 at Altrecht is feasible.

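### The primary mixed model has no treatment-team level, so the AMBIT versus FACT standard error will be too small if outcomes differ between teams; the level list is also ill-defined in two places and omits day for the ESM data

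*Protocol article*

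**What the plan says.** Section 3.1.3 of the protocol article states the primary analysis: "Multilevel (mixed) model analysis will be conducted to compare outcomes for both conditions on the OQ-45.2", with "treatment (FACT or AMBIT) as independent variable". It names no treatment-by-time term. It then fixes the hierarchy: "The different levels for the multilevel (mixed) model analysis will be: 1) participant, 2) measurement wave, 3) outcome measure, and 4) location of sampling". No analysis section mentions the team.

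Section 2.2.2 (Feasibility) counts the teams at the sites. For FACT: "GGZ Rivierduinen location Leiden has 4 FACT teams. Altrecht location Utrecht has 9 FACT teams". For AMBIT: "Rivierduinen has one AMBIT informed-MBT team, whereas Altrecht has five"; section 2.5.1.2 confirms five AMBIT-PD teams at Altrecht. Section 2.2 recruits 40 patients into each of four groups (FACT and AMBIT at each institution), through the principal therapists of the participating teams. The Rivierduinen AMBIT group is one team.

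Section 3.2 repeats the same four levels for the ESM data, directly after this: "Since ESM data of each questionnaire is nested within days and again within the measurement period (T0, T1 or T2". Section 2.3.2.9 sets 10 prompts a day for 5 consecutive days.

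**The concern.** Both treatments are ways of organising a team. Sections 2.5 and 2.6 describe team training, supervision and intervision. Patients of one team share staff, supervision and, in part, case mix, so their outcomes may be correlated. A model that treats them as independent, given location, overstates the information on the treatment effect. With half of the AMBIT arm in one team, the overstatement is larger than equal team sizes would suggest. At stake is the false-positive rate of the primary comparison.

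Three further points concern the list itself. Location has two units. *Outcome measure* is listed as a level where only the OQ-45.2 is named. The ESM list drops the day level that the preceding sentence says is needed.

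**Working it through.** **The plan's own figure.** Section 2.2.1 gives N = 135 (f = 0.25, alpha 0.05, power 90%, three measurements, three conditions). For the between-groups effect with an assumed correlation of 0.5 between measurements, a noncentral F calculation gives N = 139; power at 135 is 0.893. The final figure follows as 135 × 1.2 = 162. Neither step allows for clustering by team.

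**Inputs for the clustering check.** Group sizes are from section 2.2 (4 × 40 = 160). Team counts are from section 2.2.2 (4 + 9 FACT, 1 + 5 AMBIT). Assumed: every team counted recruits, patients split evenly within each group, and the team ICC lies between 0 and 0.10. This gives AMBIT 1 × 40 and 5 × 8, and FACT 4 × 10 and 9 × 4.44.

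**Variance inflation for a difference in mean level.** Per arm, D = 1 + ICC × (Σn²/Σn − 1).

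- AMBIT: (40² + 5 × 8²)/80 − 1 = 24 − 1 = 23, so D = 1 + 23 × ICC.
- FACT: (4 × 10² + 9 × 4.44²)/80 − 1 = 7.22 − 1 = 6.22, so D = 1 + 6.22 × ICC.
- Mean of the two equal arms: D = 1 + 14.61 × ICC.

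The true standard error divided by the one that ignores teams is √D. The type I error is 2 × (1 − Φ(1.96/√D)). The effective N is 160/D.

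| Assumed team ICC | D | SE ratio | Type I error, formula | Type I error, simulation adjusting for location | Effective N |
|---|---|---|---|---|---|
| 0 | 1.00 | 1.00 | 0.050 | 0.050 | 160 |
| 0.01 | 1.15 | 1.07 | 0.067 | 0.069 | 140 |
| 0.02 | 1.29 | 1.14 | 0.085 | 0.082 | 124 |
| 0.05 | 1.73 | 1.32 | 0.136 | 0.137 | 92 |
| 0.10 | 2.46 | 1.57 | 0.212 | 0.214 | 65 |

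The simulated column shows that a location term does not repair the omission. With 19 equal teams (160/19 = 8.4 patients each) the SE ratio at ICC 0.05 would be only √(1 + 7.42 × 0.05) = 1.17; the rest comes from unequal team sizes, chiefly the one team of 40.

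**The same check for treatment-by-time.** A stable team difference cancels from the change T2 − T0. With total variance 1 and correlation 0.5, the standard error of the difference in change is √(2 × 0.5 × (1/80 + 1/80)) = 0.158, with or without a team intercept. Simulation agrees: with a team ICC of 0.05 in level only, the SE ratio is 1.00 and the type I error 0.050. If teams differ in change, the problem returns. At an ICC of change of 0.01, 0.02, 0.05 and 0.10, the SE ratios are 1.07, 1.13, 1.33 and 1.61, and the type I errors 0.068, 0.084, 0.139 and 0.223.

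**The other levels.** Two locations leave one degree of freedom for a variance. Section 3.1.4 itself treats location as a categorical factor. Both institutions supply both treatments, so a badly estimated location variance does not itself shrink the treatment standard error. *Outcome measure* has nothing to index when one score is modelled. For ESM, 10 × 5 = 50 prompts per wave are grouped by day, and the list has no day.

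**The case against.** **The size depends on quantities the article does not give.** This stands. No ICC or team split is stated. The total of 4 + 9 + 1 + 5 = 19 is a feasibility count; a reader might take it as the number of recruiting teams, but section 2.2 refers only to participating teams. Fewer recruiting FACT teams would make clusters larger and the inflation worse.

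**The hypothesis concerns improvement, so a team intercept cancels.** This stands in part. Section 3.1.3 literally describes a treatment main effect, where level matters. If treatment-by-time is meant, the harm comes from between-team variation in change, and a random team intercept alone would not cure it.

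**All three faults in the list shrink the standard error.** A reader might infer this, but only the missing team level can. The other two make the model ill-defined.

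**Matching deals with case mix.** In part: propensity matching (sections 3.1.1 and 3.1.2) can balance observed characteristics and may reduce the analysed N below 160. It does not remove the effect of shared staff and supervision.

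***Outcome measure* might mean the OQ-45.2 subscales, or the single ESM observation.** Possible, and for ESM it would supply the prompt level, but the text does not say so, and day would still be missing.

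**Location of sampling might mean team.** Section 2.2.2 uses location for Leiden and Utrecht, as distinct from the teams within them.

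**Conclusion.** The omission is certain from the text, because the article fixes the list of levels itself. The consequence is conditional: the treatment standard error is too small if teams differ in level (main effect) or in change (treatment-by-time). Under the assumed even splits, the type I error is about 7%, 8%, 14% or 21% at a team ICC of 0.01, 0.02, 0.05 or 0.10, and stays at 5% when the ICC is zero. The documents do not support an unconditional claim that the primary test is anticonservative, nor any one of these figures as the true one.

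Location as a random level and *outcome measure* as a level are separate specification faults with no stated effect on the standard error. The ESM list contradicts the sentence before it by omitting day; its size cannot be computed, because no variance components are given.

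**What to change.** - Record the team identifier at recruitment.
- Primary model: waves within participants within teams, with a random team intercept and, for the treatment-by-time contrast, a random team-by-time term (team slope). Enter location as a fixed effect, delete *outcome measure*, and use Satterthwaite or Kenward-Roger degrees of freedom.
- ESM model: prompts within days within waves within participants, with team above.
- State that AMBIT informed-MBT is a single team, so its team and programme effects cannot be separated. In the comparison with AMBIT-PD in section 3.2, which uses the AMBIT arm only, site is confounded as well.

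The administrative cost is one extra variable and a rewritten model statement. The statistical cost may be material: on the figures above, a standard error about 7% larger at ICC 0.01 and 32% larger at ICC 0.05. A fitted random-team model gives the one large team less weight, which may recover some of this, while the small number of teams reduces the degrees of freedom.

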#### Moderating and mediating effects

3.1.4

To analyse the moderating effect of the factor variable (i.e. severity of childhood trauma and duration of illness) on treatment outcome in both treatment conditions an ANOVA will be performed, with the moderating factors, treatment condition and their interaction term as independent variables and the OQ-45.2 scores as dependent outcomes.

A linear regression analysis will be performed to investigate a potential mediating relationship between the treatment conditions and epistemic trust and reflective functioning.

Furthermore, given potential differences across locations, an exploratory moderation analyses with location as a categorical moderator will be conducted.

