##### Childhood trauma and attachment security

2.3.2.6

Childhood trauma and adversity will be assessed using the Childhood Trauma Questionnaire (CTQ) (51, 55–57), and the Youth and Childhood Adversity Scale (YCAS) (58). The CTQ is a 28-item self-report measure assessing severity of childhood abuse and neglect, and includes five subscales: 1) Emotional Abuse, 2) Physical Abuse, 3) Sexual Abuse, 4) Emotional Neglect, and 5) Physical Neglect. Items are rated on a 5-point Likert scale, ranging from 1 (*never true*) to 5 (*very often true*), with higher scores indicating greater severity. The questionnaire includes a minimization/denial scale to identify potential under-reporting of trauma, enhancing measurement accuracy and reliability. The CTQ demonstrates good reliability and validity across (clinical) populations (57).

The YCAS is a 13-item retrospective self-report questionnaire assessing exposure to adverse life events (e.g., serious illness, serious parental illness, or “other” adversity). Participants need to indicate whether they have experienced each type of adversity (yes/no). For any endorsed event, participants need to rate the perceived severity on a 7-point scale from 1 (*not at all traumatic*) to 7 (*extremely traumatic*). The YCAS has good reliability and validity (58).

Autonomy and attachment will be assessed using the Autonomy-Connectedness Scale (ACS-30) in Dutch (59, 60). The ACS-30 consists of 30 items across 3 subscales: 1) Self-awareness (awareness of one’s own opinions, desires, and needs during social interactions), 2) Sensitivity to others (empathy and consideration of others’ opinions), 3) Ability to handle new situations (comfort with unfamiliar situations, flexibility, and exploration). Items are rated on a 5-point Likert scale from 1 (*strongly disagree*) to 5 (*strongly agree*), with higher scores indicating greater autonomy and secure attachment. The measure demonstrates good reliability and validity (59).

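### Two graded moderators are worded as ANOVA factors, which on a literal reading groups them and weakens each treatment-by-moderator test

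*Protocol article*

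**What the plan says.** The last aim in the Introduction of the protocol article is a pair of moderation hypotheses: "It is expected that severity of childhood trauma, and duration of illness have a moderating effect on treatment outcome". Section 3.1.4 gives the method. It begins "To analyse the moderating effect of the factor variable (i.e. severity of childhood trauma and duration of illness) on treatment outcome" and states that "an ANOVA will be performed, with the moderating factors, treatment condition and their interaction term as independent variables", with OQ-45.2 scores as the outcome. A later sentence in the same section adds that "an exploratory moderation analyses with location as a categorical moderator will be conducted".

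Section 2.3.2.6 describes the trauma instruments. "The CTQ is a 28-item self-report measure assessing severity of childhood abuse and neglect"; its items are scored 1 to 5, higher meaning more severe, and no severity bands are given. On the YCAS, for each adversity endorsed, "participants need to rate the perceived severity on a 7-point scale". Section 3.1.4 does not say which score stands for trauma severity. The collected data named in 2.3.2.1 do not include duration of illness, though that list is not presented as complete.

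**The concern.** A factor in an ANOVA is a set of groups. A questionnaire total and a length of time are quantities, so entering them as factors means, on the plain reading, cutting each into categories first. Patients within a category are then treated as alike, and the part of the moderator that varies within categories no longer helps the interaction test.

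Both interactions are stated hypotheses. If coding has weakened the tests, a non-significant result could be reported as absence of moderation when the analysis had little chance of finding it. The point is separate from which waves or baseline terms the model holds: a well-built longitudinal model would lose the same information if the moderators stayed grouped.

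**Working it through.** **1. The plan's own figure.** The article gives no power for moderation. Its only calculation (2.2.1) is for the main comparison: f = 0.25, alpha 0.05, 90% power, three conditions, three measurements, 135 patients. For the between-groups test, λ = N·f²·m / [1 + (m − 1)ρ]. With ρ = 0.5 (assumed; not stated), λ = 135 × 0.0625 × 3 / 2 = 12.66 on 2 and 132 df, and power is 89.3%. The figure reproduces to within a point. It contains no moderator term, so it gives no assurance about 3.1.4.

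**2. Information kept after grouping.** For a linear interaction, the share kept is R² = Σ p_g(μ_g − μ)² / σ², where p_g and μ_g are the proportion and moderator mean in group g.

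- Normal, median split: group means are ±√(2/π) = ±0.798 SD, so R² = 2/π = 0.637 and 36% is lost. In these terms 160 patients act like 160 × 0.637 = 102.
- Uniform, K equal groups: R² = 1 − 1/K², so 0.75 for two groups and 0.96 for five.
- Exponential, median split: group means are 1 ± ln 2, so R² = (ln 2)² = 0.48 and 52% is lost.

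Information lost, by numerical calculation (the shapes are assumptions; the article gives no distribution):

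| Shape of moderator | Median split | Tertiles | Quartiles | Quintiles |
|---|---|---|---|---|
| Uniform | 25% | 11% | 6% | 4% |
| Normal | 36% | 21% | 14% | 10% |
| Gamma, shape 2 | 45% | 28% | 21% | 16% |
| Exponential | 52% | 35% | 26% | 21% |
| Log-normal, sigma 0.8 | 63% | 49% | 40% | 35% |

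Unequal cuts of a normal moderator lose about 43% (70/30) and 51% (80/20).

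**3. Effect on power.** A two-sided 5% test with 80% power has mean 1.96 + 0.842 = 2.802 on the z scale. After a median split of a normal moderator this becomes 2.802 × √0.637 = 2.236, and power is Φ(2.236 − 1.96) = Φ(0.276) = 61%. For tertiles, R² is 0.793, the noncentrality is 2.802² × 0.793 = 6.23 on 2 df, and power is 60%. Finer grouping keeps more information but spends more degrees of freedom, so it does not restore power.

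**4. Check by simulation.** Two equal arms, one outcome per patient, normal moderator, assumed linear interaction of 0.485 SD of outcome per SD of moderator, 4,000 runs:

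| N | Continuous | Median split | Tertile factor | Quartile factor |
|---|---|---|---|---|
| 135 | 79% | 58% | 58% | 54% |
| 160 | 85% | 68% | 67% | 64% |

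The interaction size was picked to put the continuous test near 80% at N = 135. It has no source in the article.

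**The case against.** The strongest reply is that the article never says the scores will be split, grouped or cut. *Factors* may be everyday wording for moderators. Software for ANOVA and the general linear model accepts a continuous covariate and its product with treatment, and a model with "with the moderating factors, treatment condition and their interaction term as independent variables and the OQ-45.2 scores as dependent outcomes" could be exactly that. Only location is called categorical. The coding may also be set out in the full protocol, the analysis plan or the preregistration, none of which is shown. Moderation is the last-listed aim, and no power is claimed for it.

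Much of this stands. A reader might infer that the ANOVA forces both variables into categories, that about a third of the information on each hypothesis is lost, and that the cuts will be chosen after the data are seen. The article supports none of these. A continuous covariate remains possible. The one-third figure needs a median split and a near-normal moderator, and neither is stated. Cut-points missing from an article are no finding. That duration is a graded quantity is an inference, since no measure of it is described.

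What does not fall is the wording itself. Section 3.1.4 states a method, and its usual meaning is grouping. The same section uses linear regression for mediation, and 3.1.1 separates categorical from continuous variables and assigns methods to each, so the distinction is one the authors draw. Calling location categorical does not show that the other two are continuous, because location could be nothing else. If continuous terms are intended, the sentence describes the wrong analysis and needs the same correction.

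**Conclusion.** The point holds as a fault in the stated analysis: two hypothesised moderators, one documented as graded and the other graded by nature, are worded as ANOVA factors. Read literally, this groups them and weakens each treatment-by-moderator test.

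The size is conditional. The loss of information for a normal moderator ranges from 14% to 36% between quartiles and a median split, and from 4% to 63% over all the shapes and equal-sized groupings tabulated. In power, a test near 80% with a continuous term falls to about 60% with a median split or tertiles. These figures rest on an assumed distribution, a linear interaction, one outcome per patient and an assumed interaction size. They show what grouping would cost; they do not show that it will happen.

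The primary comparison of AMBIT with FACT is unaffected. The correction is still worth making, because the hypotheses are stated, no power is given for them, and the better method costs little.

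**What to change.** In 3.1.4, replace the ANOVA with continuous moderator terms in the OQ-45.2 mixed model already planned in 3.1.3:

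- Enter trauma severity as a centred continuous term and name the score, for example the CTQ total.
- Enter duration of illness as a centred continuous term and say how it is measured, since 2.3.2.1 does not list it.
- Give each moderator its interactions with treatment and wave. The moderator-by-treatment-by-wave term then carries the hypothesis about differential change.
- Check linearity, for example with a spline.
- For readability, report the treatment effect at chosen percentiles of the moderator, such as the 25th and 75th.

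If groups are wanted for a substantive reason, define the categories in advance and say why.

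The cost is the wording of one sentence plus the naming of two measures. The software is unchanged, and so are the data, provided that duration of illness is already being recorded. The one statistical price is a linearity assumption, which can be checked.
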